# **List of Abbreviations/Terminology**

ACSM American College of Sports Medicine

ANCOVA              Analysis of covariance

ASCO American Society of Clinical Oncology

CIPN Chemotherapy induced peripheral neuropathy

CIPN-RODS Chemotherapy induced peripheral neuropathy-Rasch built Overall Disability Scale

CONSORT Consolidated Standards of Reporting Trials

CTCAE                  Common Terminology Criteria for Adverse Events

CTL Control

EORTC European Organization for Research and Treatment OF Cancer

EORTC-QLQC30 EORTC core quality of life questionnaire

ECOG Eastern Cooperative Oncology Group

ESMO European Society for Medical Oncology

EX-CIPN Exercise-based rehabilitation program

INT Intervention group

MI Motivational interviewing

MS Teams           Microsoft Teams

NCI National Cancer Institute

QoL                       Quality of life

RCT Randomized controlled trial

REB                       Research ethics board

RedCap Research electronic data capture tool

RKin Registered kinesiologist

SPIRIT Standard protocol item: recommendations for intervention trials

UC Usual care

**PROTOCOL SYNOPSIS**

| **Protocol Title** | |
| --- | --- |
| Ex-CIPN: A Phase II Trial of an exercise-based rehabilitation intervention to treat Chemotherapy Induced Peripheral Neuropathy (CIPN) | |
| **Study Detail** | |
| **Study Population/Indication (s):** | All cancers; within 6-12 months of completion of taxane or platinum-based chemotherapy; reporting persistent CIPN |
| **Study Design:** | Single-centre single-group Phase I trial |
| **Sample Size:** | 40 |
| **Estimated Accrual Duration:** | 15 months |
| **Estimated Study Duration:** | 24 months |
| **Participating Sites:** | Princess Margaret Cancer Centre, Toronto, ON, CANADA |
| **Intervention:** | EX-CIPN, a tailored progressive remotely delivered 10-week exercised based rehabilitation intervention. |

**Rationale for Study**

Improvements in early detection and the treatment of cancer have led to a substantial increase in the number of people living with a personal history of cancer. With increasing prevalence of people now surviving cancer and transitioning into the extended survival phases of cancer care, the long-term effects of cancer and its treatments and previously unrecognized chronic morbidity and related disability are of increasing importance.

Chemotherapy-induced peripheral neurotoxicity (CIPN) is a prevalent adverse effect of chemotherapy agents that is estimated to be present in 2/3 of patients who receive neurotoxic chemotherapy. In 30-40% of patients (higher for those treated with taxanes and platinum analogues), CIPN signs and symptoms such as neuropathic pain or decreased sensation can persist for months or years post-treatment. CIPN has a profound impact on the quality of life for individuals who have undergone treatment for cancer, including pain, weakness, physical disability and impairment, falls, compromised social well-being, and obstacles in returning to work after treatments are completed. Currently, there are no evidence-based approaches for preventing CIPN and symptomatic treatment options for established CIPN are limited and of uncertain benefit.

Recent evidence has shown that exercise is feasible and may be an effective intervention for different forms of peripheral neuropathy and with patients experiencing CIPN. However, professional organizations such as the American Society of Clinical Oncology (ASCO) and the European Society for Medical Oncology (ESMO) have not made any strong recommendations on the use of exercise-based interventions for the prevention or symptomatic treatment of CIPN. In its most recently updated guideline, ASCO stated that “preliminary supportive evidence” exists in favor of exercise to prevent and treat CIPN, but concluded that “no recommendation can be made” due to the lack of robust evidence and recommends that more rigorous definitive studies are needed to confirm efficacy and clarify risks. Further, there has been no study of a remotely delivered theory-based exercise-based rehabilitation intervention for the symptomatic treatment of persistent CIPN.

In response, we developed an innovative remotely delivered 10-week exercise-based rehabilitation program (EX-CIPN) for cancer survivors with persistent CIPN. As a first step, we propose a Phase I study to explore the feasibility and acceptability of the program and methods, rigorously track safety, and describe the preliminary effects of the program on clinical outcomes.

**Objectives**

***Primary Objectives***

Primary Objective 1: *To determine if EX-CIPN is feasible, acceptable and safe in cancer survivors experiencing persistent CIPN.*

Primary Objective 2: *To examine the feasibility of the study design and methods (recruitment and retention rates, feasibility of data collection and procedures).*

***Secondary Objective***

To obtain estimates of the effects of EX-CIPN on pain (primary clinical outcome), CIPN symptoms, CIPN-related disability and physiologic outcomes including upper and lower body strength, balance, gait speed, and functional capacity (secondary exploratory outcomes).

**Study Design**

The proposed study is a single centre single-group Phase I trial with patients who are experiencing persistent CIPN. All participants will receive the EX-CIPN intervention. EX-CIPN is comprised of: a progressive 10-week exercise program (aerobic, resistance and balance) supported with a mobile application (Physitrack^®^) and wearable technology (Fitbit™) to track activity; and (2) weekly brief video/telephone check-ins provided by an oncology exercise specialist who is trained in motivational interviewing. Informed by behavior change theory, the program components aim to provide patients with the knowledge and tools needed to reach and maintain their wellness and exercise goals. The remote delivery of EX-CIPN helps to barriers to accessing and providing rehabilitation and provides a cost-effective model that can be widely adopted. There will be three assessment time points throughout the study (T1, T2, T3) all including patient reported outcomes and a physiologic assessment. T1 is a baseline assessment before the intervention begins, T2 is a post-intervention assessment, and T3 is a 3-month follow-up after intervention completion.

**Study Endpoints**

The objectives will be measured by the following corresponding endpoints.

***Primary Endpoints:***

**Primary Endpoint 1: *To determine if EX-CIPN is feasible (retention and adherence), acceptable, and safe in cancer survivors experiencing persistent CIPN.***

**Primary Endpoint 2: *To examine the feasibility of the study design and methods (accrual and retention rates, feasibility of data collection and procedures).***

- Recruitment and accrual will be tracked based on CONSORT criteria^93^ through a screening log that tracks data collected from all referred and screened patients. Eligibility screening will be performed to identify eligible, consented, and eligible non-recruited individuals with non-recruitment reasons documented.

*We will define our intervention as feasible if we are able to accrue an average of five (5) participants per month.*

- Retention rates at each study time point will be monitored. Retention rates will be calculated as the proportion of recruited participants that attend each assessment time point (T1, T2, and T3). We will also examine rates of complete and missing data.

*We will define our intervention as feasible to test in a subsequent RCT if there is reasonable retention (>70%) at each study time-point, in both arms****.***

- Adherence to the intervention will be assessed through health coaching call attendance, Fitbit™ usage, and self-report completion of weekly exercise plan (determined during weekly calls).

*We will define our intervention as feasible to test in an RCT if there is reasonable adherence (>70%) to the intervention components (including Fitbit usage, call attendance, and completion of weekly exercise plans).*

- Safety will be assessed throughout the study. All adverse events will be scored on the CTCAE version 5.0 ^9^ and documented during weekly appointments and at follow-up assessments with the RKin.

*Safety of the intervention will be confirmed if <10% of participants experience serious adverse events (defined as anything above a Grade 2 of the CTCAE v5) related to participation in the study or intervention occur.*

- To evaluate acceptability and guide future program refinement, we will ask all participants to complete a post-study survey immediately after T2 to provide feedback on their experience. We will also conduct in-depth semi-structured qualitative video interviews (MS Teams) with a sub-sample of approximately 1/3 of participants following the T2 assessment (including those who improved in CIPN symptoms and those who did not improve).

*Success will be measured by high levels of treatment acceptability based on qualitative survey and interview data.*

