**3.4 Screening, Enrollment, and Data Collection**

All potential participants will be provided with information on the trial. Those who are interested will undergo a screening process to determine eligibility. Individuals who meet the study criteria and provide written consent to the study will be enrolled and assigned a study identification number and scheduled to complete an in-person baseline assessment (T1). In addition, they will receive an electronic link via Research Electronic Data Capture tools (REDCap) to the baseline set of patient reported questionnaires that will be completed prior to their initial assessment and randomization (T1). Follow-up assessments will be conducted at 10 weeks (T2) (immediate post-intervention) and 22 weeks (T3) (3 month post intervention). Survey and qualitative data will be collected at the end of the program (between T2 and T3) (see Figure 1 for study schema)

During the intervention data will be collected on adherence to the program. Data will be collected from the Fitbit and Physitrack apps showing number of workouts and amount of log-ins respectively. Health coaching call attendance and self-report completion pf the exercise plan will also be collected during weekly calls in the intervention.

To optimize retention and prevent attrition, we will ensure frequent contact and monitoring with participants^3,97^, and will use a collaborative- patient-centric approach including working individually with the patient, communication of the rationale for each phase of the study, allowing flexibility in data collection methods, and promoting shared accountability and responsibility in addressing the patients’ needs.

- 1. **Withdrawal and replacement of individual participants**

Participants will be informed that they can withdraw from the study at any time without any consequences. Participants who withdraw from the study prior to the start of the intervention will be replaced. However, participants who withdraw after intervention start will not be replaced and will be asked to share the reason for withdrawing from the study.

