**6.0 Sample Size and timeline**

While there is no overall consensus regarding appropriate sample size in a feasibility study^115^, based on a simulation of a range of sample sizes and values of standard deviation for precision of estimate (α=0.05 and power at 80%); 35-40 is at the elbow point of the curves (see Figure 3). Therefore, a sample size of 40 participants will be included in the study, which is considered large enough to examine the feasibility of the study^116,117^.

There are approx. 400-500 cancer patients who receive either platinum or taxane-based curative/(neo)-adjuvant chemotherapy per year at the Princess Margaret Cancer Centre per year. It is estimated that 30-40% of these patients will report CIPN > 6 months post-treatment^21^. Based on this, we anticipate recruiting 5-6 participants per month (See Figure 4). The study will take 15 months for accrual and 20 months for data collection.

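### Acceptability, part of a primary endpoint, is collected only after T2, with no stated route for participants who leave earlier, so the conclusion is likely to be too favourable

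*Protocol*

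**What the plan says.** The synopsis of the Protocol states Primary Endpoint 1 as: "To determine if EX-CIPN is feasible (retention and adherence), acceptable, and safe in cancer survivors experiencing persistent CIPN". Acceptability has two instruments.

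- **Survey.** The synopsis says "we will ask all participants to complete a post-study survey immediately after T2 to provide feedback on their experience". Section 5.1 repeats that every participant is asked but gives no time point.
- **Interviews.** The synopsis plans them in a "sub-sample of approximately 1/3 of participants following the T2 assessment (including those who improved in CIPN symptoms and those who did not improve"). Section 5.1 keeps the one-third fraction and the timing after T2, without the symptom criterion.

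Section 3.4 sets the window for both: "Survey and qualitative data will be collected at the end of the program (between T2 and T3"). On participants who leave after the intervention has started, the withdrawal paragraph says that they "will not be replaced and will be asked to share the reason for withdrawing from the study".

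Section 8.1 lists reasons for drop-out among the study feasibility descriptives. It assesses acceptability through thematic analysis of the interviews. Section 9.0 names high acceptability, from survey and interview data, as one of the success criteria. An unmet criterion leads to changes in the protocol before the larger trial. The outcomes table sets no criterion for acceptability in advance.

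**The concern.** Both instruments are placed at a point that a participant reaches only by staying about 10 weeks. People who dislike a program, or find it too hard, are the ones most likely to leave it. If they are not asked, acceptability is judged by a group selected partly for having accepted the program.

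Two things are at stake. The first is the Section 9.0 judgement itself. The second is the stated purpose of the acceptability work, which is to guide refinement of the program: those who left are the best source on what to change. A later analysis plan cannot repair this, because views that were never collected cannot be recovered.

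**Working it through.** **Step 1. Who has a stated route to give acceptability data?**

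| Participant | Survey | Interview | Withdrawal reason |
| --- | --- | --- | --- |
| Attends T2 | Yes, after T2 | Yes, about one third | Not applicable |
| Leaves during the 10 weeks | Addressed to every participant, but timed after T2 with no trigger at withdrawal | None stated; sorting by symptom change needs T2 data | Asked; reported under feasibility |

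The planned interview sample is about 40/3 ≈ 13 people.

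**Step 2. How many could be missing while retention still counts as a success?** Section 6.0 says "a sample size of 40 participants will be included in the study". Withdrawals before the intervention starts are replaced, so I take 40 as the number of starters. The simulation behind the 40 is in a figure that is not shown, and nothing here depends on it.

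- Synopsis, above 70%: 0.70 × 40 = 28, so at least 29 must attend and up to 40 − 29 = 11 may be lost.
- Section 9.0, 70%: 28 attend and up to 40 − 28 = 12 may be lost.

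**Step 3. How far could attenders differ from all starters?** The plan gives no acceptability figure, so there is none to reproduce. As an illustration only, let *s* be the number attending T2, *a* the number of attenders with a favourable view, and *q* the favourable share among those missing.

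- Attenders only: *a*/*s*
- All starters: [*a* + *q*(40 − *s*)]/40
- Difference: (1 − *s*/40) × (*a*/*s* − *q*)

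The documents give neither *a* nor *q*. I assume about 90% favourable among attenders and let *q* run over its whole range.

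| Attend / missing | Attenders only | *q* = 0 | *q* = 0.5 | *q* = 1 |
| --- | --- | --- | --- | --- |
| 28 / 12 | 25/28 = 89.3% | 25/40 = 62.5% | 31/40 = 77.5% | 37/40 = 92.5% |
| 29 / 11 | 26/29 = 89.7% | 26/40 = 65.0% | 31.5/40 = 78.75% | 37/40 = 92.5% |
| 32 / 8 | 29/32 = 90.6% | 29/40 = 72.5% | 33/40 = 82.5% | 37/40 = 92.5% |
| 36 / 4 | 32/36 = 88.9% | 32/40 = 80.0% | 34/40 = 85.0% | 36/40 = 90.0% |
| 40 / 0 | 36/40 = 90.0% | 90.0% | 90.0% | 90.0% |

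With 12 missing, the overstatement can reach 89.3 − 62.5 = 26.8 percentage points and the understatement 92.5 − 89.3 = 3.2. With 4 missing the limits are 88.9 − 80.0 = 8.9 and 90.0 − 88.9 = 1.1. With none missing there is no difference.

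**The case against.** Assessing acceptability at the end of a program is an ordinary design choice, and the Protocol does not contradict itself on it. Several points of the defence stand.

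- **No text excludes withdrawers.** The synopsis, Section 5.1 and the outcomes table all address the survey to every participant, and T2 can be read as fixing the time only. A reader might infer that the survey is restricted to T2 attenders. The documents do not say so; they say nothing on how an early leaver is reached.
- **The symptom criterion is not exclusive.** It asks that improvers and non-improvers be included, and Section 5.1 omits it.
- **Upward bias is not established.** It requires both that leavers are not asked and that they are less favourable than attenders. The upper bounds in the table lie above the attender figure whenever someone is missing.
- **No percentage is planned.** A reader might infer that the trial would report something like 89% where the truth is far lower. Acceptability is judged qualitatively without a threshold, so there is no stated estimate to shift.
- **Other criteria give some protection.** Drop-out through dissatisfaction counts against retention, poor engagement counts against adherence, and withdrawal reasons are collected.

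The last point softens the decision risk but does not supply the missing views. Retention shows how many left; a reason for leaving is not an assessment of the program's components, and Section 8.1 does not bring it into the acceptability analysis. If the sponsor does intend to survey everyone, the Protocol still needs to say how, so either reading calls for the same edit.

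**Conclusion.** The point holds as a gap in data collection. Followed as written, a primary success criterion would rest mainly on people who reach T2, and its conclusion is likely, though not certainly, too favourable. The stronger claims, that withdrawers are excluded by rule or that acceptability is biased upward as a matter of fact, are not supported.

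The size depends on attrition before T2, which is unknown. At the retention limits 11 or 12 of 40 could be missing, and the illustrative overstatement is at most about 27 points against an understatement of about 3. If nearly all 40 reach T2, little is lost. These percentages rest on an assumed attender figure near 90% and on leavers giving no acceptability data; they show scale and are not predictions. The change is worth making because it is cheap and cannot be made after the data are in.

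**What to change.** In the synopsis and in Sections 3.4 and 5.1:

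1. Send the existing survey through REDCap at withdrawal, or at week 10 regardless of T2 attendance, to everyone who started EX-CIPN.
2. Within the planned one-third interview sample, keep some places for willing participants who withdrew or had low adherence, alongside the sampling on symptom change.
3. Report the number of respondents out of all starters, and set the withdrawal reasons beside the acceptability result. No per-person acceptability score is needed.

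The cost is some wording and one extra survey trigger. No interviews are added. Some withdrawers will not respond, though that non-response becomes visible. A few of the roughly 13 interview places move from completers to others, and the result may look less favourable.

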***Secondary Endpoints***

**Secondary Endpoint 1: Reduction in the patient-reported CIPN-related pain (primary clinical outcome) will be summarized in the intervention and control groups.**

*Calculation of the sample size for a larger RCT will be based on distribution of change observed in this pilot and a minimally important clinical change of 2 points on the numeric pain rating scale from T1-T3 assessment.*

Secondary Endpoint 2: Estimates of the effect of the EX-CIPN intervention on CIPN symptoms, CIPN-related disability and physiologic outcomes including upper and lower body strength, balance, gait speed, and functional capacity (exploratory secondary outcomes).

**Abbreviated Eligibility Criteria**

***Main Inclusion Criteria***

- 18years of age
- Received a diagnosis of any cancer and treated with curative intent (no minimum dose) including Stage 3 & 4 gynecologic malignancies, treated in the platinum-sensitive setting
- Are within 6-12 months of completion of taxane or platinum-based chemotherapy (ie no other chemotherapeutic agents since completing of the chemotherapy regimen)
- Report > Grade 1 on the Patient Reported NCI Common Terminology Criteria for Adverse Events version 5.0 grading scale (numbness and tingling severity item) and neuropathic pain >3 on the DN4 (interview) (0-7)
- The presence of peripheral neuropathy due to chemotherapy (following onset of chemotherapy), as established via clinical assessment.
- May be on maintenance oncologic therapies (ie endocrine therapy, PARP inhibitors) not known to cause neuropathy
- No current plans for chemotherapy in the next 6 months
- Currently engaging in < 90min per week of planned moderate-intensity aerobic exercise
- Independent with ambulation and transfers with or without ambulatory assistance (EGOG 0-2)
- Able to communicate sufficiently in English to complete intervention, questionnaires, and consent
- Willing to participate in the intervention and attend in-person physical assessments
- Have access to and are able to operate videoconferencing.

***Exclusion Criteria***

- Known neurological conditions influencing cognition and preventing safe or appropriate engagement with self-management and exercise recommendations
- Individuals currently using TDM1 adjuvant hormone therapy
- Pre-existing neuropathy prior to the start of chemotherapy
- Currently enrolled in other cancer rehabilitation or exercise-based programs/interventions.

**
[figure not shown]
**

**STATEMENT OF COMPLIANCE**

This study will be conducted in compliance with the protocol, International Conference on Harmonisation [ICH] E6, applicable regulatory requirements, and carried out in accordance with Good Clinical Practice (GCP) as per the following:

- Tri-Council Policy Statement: Ethical Conduct for Research Involving Humans, Canadian Institutes of Health Research, Natural Sciences and Engineering Research Council of Canada, Social Sciences and Humanities Research Council of Canada
- Personal Information Protection and Electronic Documents Act [PIPEDA]

All key personnel (all individuals responsible for the design and conduct of this study) have completed GCP/Human Subjects Protection Training.

**1.0 OBJECTIVES**

**1.1 Primary Objectives**

- Primary Objective 1: *To determine if EX-CIPN is feasible, acceptable and safe in cancer survivors experiencing persistent CIPN.*
- Primary Objective 2: *To examine the feasibility of the study design and methods (recruitment and retention rates, feasibility of data collection and procedures).*

**1.2 Secondary Objective**

- Secondary Objective: *To obtain estimates of the effects of EX-CIPN on pain, CIPN symptoms, CIPN related disability and physiologic outcomes including upper and lower body strength, balance, gait speed, and functional capacity.*

**2.0 BACKGROUND and Rationale**

Improvements in early detection and treatment of cancer have led to a substantial increase in the number of people living with a personal history of cancer^10^. In 2018, there were an estimated 43.8 million cancer survivors diagnosed within the previous 5 years worldwide and this number is expected to grow by close to 25% over the next decade^11^. With increasing proportions of people now surviving cancer and transitioning into the extended survival phases of cancer care, the long-term effects of cancer and its treatments and previously unrecognized chronic morbidity and related disability are of increasing importance^12,13^.

Chemotherapy is a necessary component to increase the cure of many common cancers; however, it can induce changes to cellular structure and functions resulting in toxic effects ^14^. Chemotherapy-induced peripheral neurotoxicity (CIPN) is a prevalent adverse effect of adjuvant/curative chemotherapy agents^15-17^ which can develop at any point during chemotherapy receipt or occasionally after treatment completion^18^. CIPN is estimated to be present in 2/3 of patients who receive neurotoxic chemotherapy. Acute CIPN generally improves over the first 3-6 months following treatment completion^19,20^. However, in 30-40% of patients (higher for those treated with taxanes and platinum analogues), CIPN signs and symptoms such as neuropathic pain or decreased sensation can persist for months or years post-treatment^19,21-24^ .

While the exact pathogenesis of CIPN is unknown, CIPN is considered a predominately sensory neuropathy that typically affects distal limbs but can also be accompanied by motor neuropathy manifesting as weakness and autonomic neuropathies which may impact cardiovascular performance^25^. The sensory involvement of CIPN can result in pain, numbness, paresthesia (tingling, burning sensation), temperature sensitivity and/or proprioception^26^. These symptoms can lead to statis and dynamic instability, gait disturbances, and increased appendicular muscle weakness, resulting in physical deconditioning and an increased risk of falls. The risk of falls in cancer patients with CIPN is almost double compared to individuals without CIPN^27^. **Therefore, CIPN has a profound impact on the quality of life for individuals who have undergone treatment for cancer, including pain, weakness, physical disability and impairment, falls, compromised social well-being, and obstacles in returning to work after treatments are completed**^28-33^**.**

Currently, there are no evidence-based approaches for preventing CIPN^34^ and symptomatic treatment options for established CIPN are limited and of uncertain benefit^35-38^. Pharmacological agents that are effective for the symptomatic treatment of diabetic and HIV-related neuropathies, such as tricyclic antidepressants and antiepileptic drugs, have generally yielded negative results with CIPN^37-40^ and require more caution when used for older adults with cancer^41^ . Duloxetine is currently the only recommended pharmacological agent for the symptomatic treatment of CIPN^35^, though its benefit is limited and studies have not compared its use across all types of cancer or neuropathy causing agents^35^. Other neurological agents including gabapentin and pregabalin have also been tested to prevent or treat CIPN in clinical trials, but the results have not supported their use and their use is not recommended outside clinical trials^42^. These medications can result in side effects including dry mouth, constipation, diarrhea, and dizziness^43^. Further, their use may be contraindicated with tamoxifen, a common endocrine therapy in women with breast cancer. Given the lack of benefits and side effects of pharmacologic therapies along with cancer survivors’ desire to limit any further required medication^44^, research examining a wide range of non-pharmacologic interventions has emerged^45^. Of these, the most recent evidence suggests that physical therapy/exercise and acupuncture may reduce CIPN symptoms including pain^35,45,46^; however, larger definitive studies are needed to confirm the efficacy and clarify the risks of these interventions^35^.

Exercise-based rehabilitative interventions are effective for managing common side effects of treatment and enhancing functional abilities in individuals affected by cancer, both during and after treatment^47,48^. Recent evidence has also shown that exercise is feasible and may be an effective intervention for different forms of peripheral neuropathy^1,2^ and for patients experiencing CIPN^3-7^. Exercise may potentially alleviate peripheral neuropathy through several neurophysiological mechanisms in the peripheral and central nervous systems, including the induction of an anti-inflammatory environment, increasing the supply of blood, glucose and oxygen to mitochondria, and by affecting psychosocial processes^49-52^. Observational trials have demonstrated connections between higher levels of physical activity and milder cases of CIPN ^53,54^. Preliminary evidence on exercise-based rehabilitation symptomatic interventions for the treatment of established CIPN, while modest and heterogeneous in terms of the intervention protocols tested and outcomes measured, demonstrate encouraging positive effects on CIPN-related outcomes^3-7^. However, professional organizations such as the American Society of Clinical Oncology (ASCO) and the European Society for Medical Oncology (ESMO) have not made any strong recommendations on the use of exercise-based interventions for the prevention or symptomatic treatment of CIPN. **In its most recently updated guideline, ASCO stated that “preliminary supportive evidence” exists in favor of exercise to prevent and treat CIPN, but concluded that “no recommendation can be made” due to the lack of robust evidence and recommends that more rigorous definitive studies are needed to confirm efficacy and clarify risks^35^.**

To date, the evidence on exercise intervention for the prevention and symptomatic treatment of CIPN is limited by low study quality, lack of homogeneous patient population, and a lack of definitive rigorous trials with CIPN pain and symptoms as the primary end-point^2,4,7^. Further, the incorporation of behaviour change theory and related behaviour change techniques is recommended in the development and evaluation of rehabilitation interventions that require patient’s to adopt health-related behaviours^55^; however, a recent review of exercise interventions for the prevention and management of CIPN found that no study has incorporated a clear theoretical or conceptual framework related to behaviour change^56^.

Traditional supervised exercise-based rehabilitation interventions for people with cancer have been facility-based (e.g. hospital or university). Over the past decade an increasing number of supervised virtual exercise-based interventions^57^ have been shown to be safe, feasible, and effective^58-60^. These arose in response to well-documented patient barriers to attending facility-based programming, including the lack of locally available cancer-exercise programs, inflexible program hours, costs, time associated with transportation, and symptom burden^61-64^. Most people with cancer report a preference for exercising at home, if provided with appropriate support and guidance from a qualified oncology exercise professional^63,65^ and evidence demonstrates good compliance and positive experience with virtual platforms for exercise delivery^66^. The majority of exercise studies for the prevention or symptomatic treatment of CIPN have been delivered in supervised settings^67^. **There has been no study of a remotely delivered theory-based exercise-based rehabilitation intervention for the symptomatic treatment of persistent CIPN.**

In response, we developed an innovative remotely delivered 10-week exercise-based rehabilitation program (EX-CIPN) for cancer survivors with persistent CIPN. As a first step, we propose a Phase I study to explore the feasibility and acceptability of the program and methods, establish safety, and describe the preliminary effects of the program on clinical outcomes.

